### 561 ***Blinding***

562 Blinding is described in section 0.

563 Blinding will be recorded in a blinding log – on this log, blinded and unblinded study team  
564 members will be tracked. If there is an isolated break in the blind that/those member(s) of the  
565 research team must be transferred to the unblinded team.

566 For purpose of clarity, the un-blinded and blinded personnel is listed in the following table.

| Un-blinded                                                                         | Blinded                                                                                                                                                                                                                                                                                                                                                                                                                                                    |
|------------------------------------------------------------------------------------|------------------------------------------------------------------------------------------------------------------------------------------------------------------------------------------------------------------------------------------------------------------------------------------------------------------------------------------------------------------------------------------------------------------------------------------------------------|
| 

• Implantation operation room Team

 | 

• ICU team, undertaking Safety Assessments, TCD readings and GCS assessments and angiograms and computer tomography scans for patient management decisions.

• Independent specialist undertaking analysis of the angiograms and CT/MRI brain scans for the diagnosis of vasospasm and new cerebral infarcts.

• Trained personnel collecting data on clinical outcome and mortality week 12

 |

|  |                                                                                                                                                                  |
|--|------------------------------------------------------------------------------------------------------------------------------------------------------------------|
|  | 
and week 52.
 
 
Independent experts adjudicating on the presence of DIND and anti-vasospasm rescue therapy
 
 |
|--|------------------------------------------------------------------------------------------------------------------------------------------------------------------|

567

568

## 569 **Treatment compliance**

570 NicaPlant® is implanted once (at the time of aneurysmal clipping); therefore, there are no  
571 treatment compliance issues.

572 Blood samples are collected for safety and pharmacokinetic measurements at fixed time  
573 points. Compliance will be monitored throughout the study.

## 574 **Drug storage**

575 All study medication will be stored at 2 - 8°C protected from light in the storage area, which  
576 will be a secure, temperature controlled, locked environment with restricted access.

577 No special procedures for the safe handling of NicaPlant® are required. The Sponsor will be  
578 permitted upon request to audit the supplies, storage, dispensing procedures and records  
579 provided that the blind of the study is not compromised.

## 580 **Drug accountability**

581 In accordance with GCP, the clinical unit will account for all supplies of NicaPlant®. Details  
582 of receipt, storage, assembly and return will be recorded.

583 All unused supplies of NicaPlant® will either be destroyed or returned to the study Sponsor at  
584 the end of the study in accordance with instruction by the Sponsor.

585

## 586 **STUDY PLAN**

### 587 **Study Timings**

588 Timing in the study is measured from time of aneurysm rupture; as the time of rupture cannot  
589 be determined precisely it shall be defined as the time from onset of first symptoms.

### 590 **Continuous Assessment**

591 The following assessments will be carried out on a continuous basis and as events arise:

592 Adverse Events and separately, bacterial meningitis and shunt-dependent hydrocephalus.

593

594 **Visit 1: Pre-implantation assessment (within 48 hours of aneurysm rupture and SAH)**

595 The following assessments will be performed and documented in all patients admitted with a  
596 diagnosis of spontaneous aneurysmal SAH and consented appropriately to the study:

- 597 • Inclusion/Exclusion Criteria (screening failures to be recorded)
- 598 • Angiography (DSA) of the ICA bilateral and both vertebral arteries
- 599 • CT of the brain
- 600 • Demographics/Medical History
- 601 • Physical examination
- 602 • Pregnancy test
- 603 • Vital signs (blood pressure, pulse rate, respiratory rate, temperature)
- 604 • ECG
- 605 • Haematology, serum biochemistry
- 606 • mGCS
- 607 • Randomisation
- 608 • Informed consent procedure according to section 14

609  
610 The assessments for the participation in the study shall not cause any delay in the  
611 treatment of the patients. The safety and wellbeing of the patients needs to be the main  
612 focus all the time.

613  
614 **Visit 2: Clip Ligation & Implantation (within 72 hours of aneurysm rupture)**

615 Eligible patients will be randomised to either NicaPlant® implantation or no implantation.

- 616 • Clip ligation
- 617 • Implantation (if randomised to the study group) of NicaPlant® implants
- 618 • PK Plasma sampling (0, 6, 12, 24 hrs after implant,  $\pm 20$  minutes each)
- 619 • CSF sampling (patients with EVD and CSF sampling performed for standard of care  
620 only)
- 621 • CT brain scan, post-surgery,  $36 \pm 12$  hours from clip ligation (on NicaPlant®  
622 application) to identify surgery related ischemic lesions and for baseline assessment.

623  
624 **Ongoing Assessments (day of surgery to day of patient discharge or day 21 $\pm$ 1 post**  
625 **aneurysm, whichever occurs first)**

626  
627       • Daily – mGCS, TCD reading for evidence of vasospasm (to be confirmed by DSA),  
628       CSF sampling (patients with EVD in days when CSF sampling is performed for  
629       medical reasons only), PK Plasma sampling on days blood is drawn for medical  
630       reasons but only once per day (time of sampling to be recorded).

631  
632 **Visit 3: Angiography (DSA) (day 8±1 post aneurysm rupture or whenever vasospasm is**  
633 **suspected by sonographic or clinical means).**

634       • Angiographic assessment for vasospasm (even if no clinical evidence is present); if  
635       the patient develops clinical or sonographic changes suggestive of vasospasm prior to  
636       day 8, an angiogram will be performed to confirm the vasospasm and the  
637       angiographic measurement will replace the one scheduled at day 8±1 (Visit3). Both  
638       ICA and the dominant vertebral artery should be documented.

639  
640       • PK Plasma sampling (time of sampling to be recorded).

641       • vital signs (BP, pulse rate, respiratory rate, temperature), ECG, haematology, serum  
642       biochemistry

643  
644 **Visit 4: before patient discharge or day 14±1 post aneurysm rupture, whichever occurs**  
645 **first**

646       • CT brain scan, for assessment of new cerebral infarcts.

647       • PK Plasma sampling (time of sampling to be recorded).)

648       • vital signs (BP, pulse rate, respiratory rate, temperature), ECG, haematology, serum  
649       biochemistry

650  
651 **Visit 5: day of patient discharge or day 21±1 post aneurysm, whichever occurs first**

652       • PK Plasma sampling (time of sampling to be recorded).).

653       • vital signs (BP, pulse rate, respiratory rate, temperature), ECG, haematology, serum  
654       biochemistry

655       • Modified Rankin Scale (mRS)

656  
657 **Visit 6: Week 12 post aneurysm rupture**

658       • Modified Rankin Scale (mRS)

659       • extended Glasgow Outcome Scale (GOSE)

660       • Montreal Cognitive Assessment tool (MoCA)

- 661 • Health related quality of life assessed using the EQ-5D-5L and SF36
- 662 • Mortality due to SAH

663

664 **Visit 7: Week 52 post aneurysm rupture (Data to be reported in a CSR addendum)**

- 665 • Modified Rankin Scale (mRS)
- 666 • extended Glasgow Outcome Scale (GOSE)
- 667 • Montreal Cognitive Assessment tool (MoCA)
- 668 • Health related quality of life assessed using the EQ-5D-5L and SF36
- 669 • Mortality due to SAH

670

671

672 **STUDY PROCEDURES / EVALUATIONS**

673 **Safety Measurements**

674 The following safety parameters will be recorded according to the trial protocol:

- 675 • Adverse events (AEs)
- 676 • Shunt-dependent hydrocephalus
- 677 • Bacterial meningitis
- 678 • Change in grading of AE severity
- 679 • Vital Signs: blood pressure, pulse rate, respiratory rate and body temperature
- 680 • Electrocardiogram (ECG)
- 681 • Full blood count, urea and electrolytes, liver function tests, C-reactive protein

682 **Efficacy Measurements**

683 The following efficacy parameters will be recorded according to the trial protocol:

- 684 • Incidence of moderate to severe cerebral angiographic vasospasm assessed by digital subtraction angiography (DSA) within at  $8 \pm 1$  days after aneurysm rupture where angiographic vasospasm is defined as a  $\geq 33\%$  reduction in diameter in at least one vessel segment by comparison to preoperative (pre NicaPlant® implantation) angiography and/or qualitatively assessed as moderate to severe vasospasm (in case the baseline measurement is missing). A day  $8 \pm 1$  angiogram will be performed even if the patient has no clinical or sonographic evidence of vasospasm.

691 If the patient develops clinical or sonographic changes suggestive of vasospasm prior  
 692 to day 8, and angiogram (DSA) will be performed to confirm the vasospasm and the  
 693 angiographic measurement will replace the one scheduled at day  $8 \pm 1$ . In case the  
 694 patient develops clinical or sonographic changes suggestive of vasospasm after the

day 8±1 and prior to patient discharge or day 21, an angiogram (DSA) will be performed to confirm the vasospasm, unless this is not clinically indicated.

## **Secondary endpoint**

1. Incidence of new cerebral infarcts on CT scan at day 14 ± 1, or before patient discharge (compared with postoperative CT scan).

## **Other exploratory endpoints**

- Incidence of vasospasm-related morbidity/mortality within 14 days post-aneurysm rupture, or before patient discharge, defined by at least one of the following:
  - a) DIND
  - b) Death caused by vasospasm, delayed ischemic neurological deficit (DIND), infarcts or complications due to anti-vasospasm therapy
  - c) The need for anti-vasospasm rescue therapy within patient discharge
- Daily assessment of modified Glasgow Coma Scale (mGCS) up to patient discharge or day 21.
- Clinical outcome at Weeks 12 & 52 post-aneurysm rupture as measured by:
  - Modified Rankin Scale (mRS)
  - Glasgow Outcome Scale (Extended) (GOSE)
  - Montreal Cognitive Assessment tool (MoCA)
  - Health related quality of life assessed using the EQ-5D-5L and SF36
  - Mortality due SAH

## **Pharmacokinetic (PK) and Pharmacodynamic (PD) Measurements**

The following PK and PD parameters will be recorded according to the trial protocol:

### ***PK:***

PK blood sampling will be carried out in all patients on day of clip ligation at 0, 6, 12 & 24h post clipping and on days 8, 14 and day of discharge or day 21 after aneurysm rupture. Additionally PK blood sampling will be done when blood is collected for medical reasons but only once per day; only samples collected in patients treated with NicaPlant® will be analysed at the end of this study.

Whole blood samples (2 mL) will be collected into a Li-heparin tube and processed for plasma.

Samples will be collected, labelled, processed, stored and shipped as detailed in the Study Operation Manual.

Cerebrospinal fluid samples (500µL) will be collected in patients with EVD whenever CSF removal is performed for standard of care.

### ***PD:***

The pharmacodynamic endpoints are incidence of moderate to severe angiographic measurements of cerebral vasospasm and new cerebral infarcts as assessed by the independent neuroradiologist and DIND.

734 **Definitions of Assessments**

735 *World Federation of Neurological Surgeons Grading System for Subarachnoid*  
736 *Haemorrhage (WFNS)*

737 The WFNS is a 5-point scale that is a simple, reliable and clinically valid way to grade a  
738 patient with aSAH. This system offers less inter-observer variability than some of the earlier  
739 classification systems.

740 The grading is based on the Glasgow coma score (GSC see later description).

741 Grade 1            GCS score of 15 without focal deficit

742 Grade 2            GCS score of 13 or 14 without focal deficit

743 Grade 3            GCS score of 13 or 14 with focal deficit

744 Grade 4            GCS score of 7-12

745 Grade 5            GCS score of 3-6

746 *Assessment of Cerebral Vasospasm and New Cerebral Infarct by a Centralised*  
747 *Neuroradiologist Efficacy Assessment.*

748 All angiograms and computed tomography of the brain are to be evaluated locally for patient  
749 management decisions based on the local standard procedures.

750 For the assessment of the efficacy of NicaPlant® for the endpoint analysis, angiograms and  
751 computed tomography scans of the brain are to be analysed by an independent blinded  
752 neuroradiologist.

753 For this purpose, diameters of the proximal vessel segments (C1, M1, A1, P1, BA see  
754 diagram below) are to be measured in the baseline and the follow-up angiograms. To  
755 overcome potential bias from angiograms with different magnifications, the following  
756 procedure will be used:

- 757            1. The angiograms are to be optically magnified 5× to measure different vascular  
758            sections more precisely.
- 759            2. Measurements are performed on an arterial filling image in the lateral view for C1 and  
760            C5 and AP view for the other vessel segments.
- 761            3. Diameters (i.e. the contrast agent filled compartment of the vessel) are to be measured  
762            digitally in absolute values.
- 763            4. A ratio is to be built between all intradural and one extradural proportion (C5) of the  
764            vessel tree (as established by Weir and co-workers).

---


5. The ratios are to be used to analyse vessel diameters independently from the original magnification used. Angiographic vasospasm is defined as a  $\geq 33\%$  reduction in diameter in at least one vessel segment.
6. Angiographic vasospasm will be also assessed qualitatively as: none/mild (can be more than two major cerebral arteries [segments] with mild (less than 1/3 arterial narrowing) angiographic vasospasm and/or 1 segment with moderate angiographic vasospasm (1/3 to 2/3 arterial narrowing); moderate (at least 2 segments with moderate angiographic vasospasm and/or 1 or 2 segments with severe angiographic vasospasm [more than 2/3 arterial narrowing]); or severe (at least 3 segments with severe angiographic vasospasm). A segment corresponds to a major cerebral artery.
7. Additionally, a semiquantitative rating of the distal vessel segments according to this scheme will be performed.

[figure not shown]

Nomenclature of the basal cerebral arteries of the circle of Willis. ACA, anterior cerebral artery (segments A1, A2); ACoA, anterior communicating artery; BA, basilar artery; CS, carotid siphon (segments C1-C3); ICA, internal carotid artery; MCA, middle cerebral artery (segments M1, M2); OA, ophthalmic artery; PCA, posterior cerebral artery (segments P1, P2); PCoA, posterior communicating artery; VA, vertebral artery.

All CT examinations will be assessed by a neuroradiologist blinded to the clinical data and treatment assignment. Infarct(s) on the CT brain scan performed  $36 \pm 12$  hours postoperatively will be classified as surgery related and related to the respective vessel territory. New infarcts (compared to such postoperative CT) in the CT scan at visit 4 will be classified as vasospasm related and related to the respective vessel territory or to hemodynamic infarction.

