## 263 *Efficacy:*

### 264 **Primary efficacy endpoint**

- 265 • Incidence of moderate to severe cerebral angiographic vasospasm after aneurysmal  
266 subarachnoid haemorrhage, where angiographic vasospasm is defined as a  $\geq 33\%$   
267 reduction in diameter in at least one vessel segment by comparison to preoperative  
268 angiography.

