#### **Exclusion criteria**

1. SAH due to other causes (e.g. trauma, fusiform or mycotic aneurysm).
2. World Federation of Neurosurgery (WFNS) grade I, II and V patients.
3. Pregnant or Lactating Women.
4. Intraventricular or intracerebral blood, in the absence of subarachnoid blood.
5. Treatment of aneurysm via endovascular embolisation.
6. Presence of moderate or severe vasospasm on screening angiography.
7. Any known or CT /MRI evidence of previous major cerebral damage
8. Evidence of a cerebral infarction with neurological deficit on pre-treatment CT/MRI.
9. History of malignant disease (except for non-melanoma skin cancer) within the previous 5 years or any history of malignant brain tumours or brain metastasis.
10. Patients who have received an investigational product or participated in another interventional clinical study within 30 days prior to randomisation.
11. Patients with known allergy for Poly(D,L-lactide-co-glycolide) (PLGA) or nicardipine.
12. Major complication during aneurysm repair such as, but not limited to, massive intraoperative haemorrhage, brain swelling, or inability to secure the ruptured aneurysm.

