### 1124 ***Data Descriptions:***

1125 Data will be summarised according to patient population (FAS/PP/Safety), dose group (10  
1126 Implant/Control), assessment (Visit 1-6 / day where appropriate) and time (where  
1127 appropriate). Data collected on visit 7 will be reported and analysed in an addendum to the  
1128 study report.

1129 Categorical variables will be summarised as proportions (with 95% Clopper-Pearson  
1130 confidence intervals) and frequencies (if appropriate) and as odds ratios (with 95% Wald  
1131 confidence intervals), where logistic regression models are used. Continuous variables will be  
1132 summarised as Least square means and 95% confidence intervals, where analysis of variance

1133 (ANOVA) models are used and then also as supporting descriptive statistics (n, mean,  
1134 median, standard deviation, minimum, and maximum). Graphical displays appropriate to  
1135 these types of data will be used to present important findings.

1136 ***Treatment Group Comparability:***

1137 Surgical details (including Clip ligation & Implantation) and measures at baseline (including:  
1138 demographics, medical history, concomitant medication, physical examination, pregnancy  
1139 test) will be summarised descriptively by treatment group (10 Implant/Control) and overall.  
1140 No formal comparisons of the treatment groups at baseline will be made.

1141 ***Efficacy Endpoints:***

1142 The primary efficacy endpoint is the incidence of cerebral angiographic vasospasm (moderate  
1143 or severe) at Day 8±1. This is considered a binary outcome and the difference between the 10  
1144 Implant and Control groups will be investigated using Fishers Exact test. Proportions in the  
1145 two groups with 95% Clopper-Pearson confidence intervals will be used to quantify the  
1146 magnitude of the difference. In case cerebral vasospasm (moderate or severe) is occurring  
1147 before day 8, this measurement will replace the assessment at day 8±1.

1148 A supporting Ordinal logistic regression model (utilising all classified categories) will also be  
1149 used to provide odds ratio estimates (+/-95% confidence intervals) for the treatment effect  
1150 and associated significance levels (p-values).

1151 Secondary endpoints include the:

1152 -Incidence of new cerebral infarcts on CT scan at day 14±1, or before patient discharge,  
1153 (compared post-treatment CT scan).

1154 Exploratory endpoints include the:

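### The primary endpoint label 'moderate to severe' vasospasm carries two thresholds, and which one applies depends on whether a baseline measurement exists

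*Protocol*

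**What the plan says.** Section 2 (Primary efficacy endpoint) labels the endpoint "Incidence of moderate to severe cerebral angiographic vasospasm after aneurysmal" subarachnoid haemorrhage and defines vasospasm as a 33% or greater "reduction in diameter in at least one vessel segment by comparison to preoperative" angiography. In section 8, step 5 of the central neuroradiologist's procedure repeats the rule: a 33% or greater "reduction in diameter in at least one vessel segment".

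Step 6 of that procedure adds a three-level qualitative grade. Its none/mild level may include "1 segment with moderate angiographic vasospasm (1/3 to 2/3 arterial narrowing); moderate (at least 2 segments with moderate angiographic vasospasm" and/or one or two segments narrowed by more than two thirds. Severe needs at least three segments narrowed by more than two thirds.

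Section 8, under both Efficacy Measurements and Radiology, restates the 33% rule and then appends the grade: "and/or qualitatively assessed as moderate to severe vasospasm (in case the baseline measurement is missing").

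Section 11 (Efficacy Endpoints) uses only the label, as in "The primary efficacy endpoint is the incidence of cerebral angiographic vasospasm (moderate" or severe) at Day 8±1, without pointing to either rule. It then adds: "A supporting Ordinal logistic regression model (utilising all classified categories) will also be" used. Exclusion criterion 6 uses the same label, also without a pointer: "Presence of moderate or severe vasospasm on screening angiography".

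**The concern.** The endpoint's name matches the grade names in step 6, but the endpoint's definition is the rule in step 5, and the two disagree for one kind of patient. The second scale is more than descriptive, because the section 8 text makes it decide the primary outcome when there is no baseline measurement. Patients would then be judged against different thresholds within one binary endpoint.

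The link itself is also ambiguous. 'And/or' does not fit a parenthesis that confines the grade to missing baselines.

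The supporting ordinal model raises a related problem. Step 6 is the only patient-level ordered vasospasm scale that the protocol defines; step 7 rates distal segments, not patients. On that scale some primary events would fall in the lowest category.

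With 20 patients per arm, a single reclassified patient can decide the result. A choice between the rules made after the images are read could also look data-driven.

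**Working it through.** **1. The two rules side by side**

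| Pattern at follow-up | 33% rule (section 2; step 5) | Grade (step 6) |
|---|---|---|
| All segments below one third | no event | none/mild |
| Exactly one segment at 1/3 to 2/3, none beyond | event | **none/mild** |
| Two or more segments at 1/3 to 2/3, none beyond | event | moderate |
| Any segment beyond 2/3 | event | moderate or severe |

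Only the second row is discordant, apart from the trivial gap between 33% and 1/3. Every patient graded moderate or severe also meets the 33% rule, but not the reverse. So where a baseline exists, 'or' reduces to the 33% rule and 'and' reduces to the stricter grade.

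**2. The plan's own power figure**

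Inputs from section 11 (Power & Sample size): 20 per arm, 20% active, 70% control, Fisher's exact test, two-sided 5%, stated power 84%.

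Power = Σₐ Σ꜀ Bin(a; 20, 0.20) × Bin(c; 20, 0.70) × 1[Fisher p(a, c) ≤ 0.05] = **84.6%**. The stated figure reproduces.

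**3. Effect of the fallback**

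Take 20% and 70% as rates under the 33% rule. Let f be the share of events with exactly one segment at 1/3 to 2/3, and m the share of patients without a baseline measurement. If f is equal in both arms and baselines are missing independently of outcome, each rate becomes p × (1 − m × f). The protocol gives neither f nor m; f = 30% is an assumption.

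| m | 1 − m × 0.30 | Active | Control | Exact Fisher power |
|---|---|---|---|---|
| 0 | 1.000 | 20.0% | 70.0% | 84.6% |
| 5% | 0.985 | 19.7% | 68.95% | 83.5% |
| 10% | 0.970 | 19.4% | 67.9% | 82.5% |
| 20% | 0.940 | 18.8% | 65.8% | 80.3% |

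If the shares differ between arms, power can move either way. With m = 10%:

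- f = 30% in control only: 20% versus 0.70 × 0.97 = 67.9%, power 81.1%.
- f = 30% in active only: 0.20 × 0.97 = 19.4% versus 70%, power 85.8%.

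**4. How much one patient can matter**

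With 20 per arm, 4 versus 11 events gives Fisher p = 0.048, and 4 versus 10 gives p = 0.096.

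**The case against.** The strongest reply is that the protocol does state its endpoint. Section 2, step 5, Efficacy Measurements and Radiology all give the single-segment 33% rule, and the background section gives the same threshold. Step 6 is introduced as an additional assessment. The parenthesis confines it to missing baselines, and section 11 merely shortens the label. Baseline DSA is a Visit 1 procedure, and angiographic confirmation of the aneurysm is an inclusion criterion, so missing baselines should be uncommon, although no rate is given. All of this stands, and it keeps the problem small.

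A stricter threshold for a visual grade made without a reference film could also be defended. The evidence in the two situations is indeed not the same: one is a measured ratio against a preoperative film, the other a visual judgement. But the protocol gives no such reason, and the same label covers both thresholds.

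The choice of scale for a supporting model is commonly left to the SAP, and a supporting model may use other cut-points. That is fair: the ordinal model alone would not be an error. It belongs here because the only patient-level scale on offer does not nest the primary event.

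A reader might infer that step 6 is the endpoint for every patient. With f = 30% the rates would be 14% and 49%, and power 58.2%. No section says this, and the figure also needs the assumed equal share; unequal shares under that reading give anything from 38.5% (20% versus 49%) to 85.5% (10% versus 56%). A reader might also infer that the 20% and 70% planning rates are wrong. Section 11 ties them to the primary endpoint, which section 2 defines by the 33% rule. Which definition the cited earlier trial used cannot be checked from this document.

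**Conclusion.** The inconsistency is real and lies within the primary endpoint: one label, two thresholds, with the threshold switching on the availability of a baseline measurement. It affects patients who lack that measurement and have exactly one segment narrowed by one to two thirds.

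The 33% rule appears to be intended. Under the fallback reading the cost is about 1 to 2 points of power at 5% to 10% missing baselines, and about 4 points at 20%. These figures rest on an assumed 30% single-segment share, equal in both arms, and no general loss of power is established. The case for correction rests on the definition and on the trial's sensitivity to single patients. It should be fixed, but it does not undermine the design.

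**What to change.** - In section 2, both section 8 texts and section 11, state that the primary event is at least one segment narrowed by 33% or more.
- Replace 'and/or' with an explicit fallback, used only when the baseline measurement is missing, with the same threshold: at least one segment visually narrowed by one third or more.
- Name the scale for the ordinal model and cut it so that its lowest boundary is the primary event. For example: no segment at or above one third; at least one segment at one to two thirds and none beyond; at least one segment beyond two thirds.
- Keep the step 6 grade as a descriptive scale under a different name.
- Say which scale exclusion criterion 6 refers to.

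The cost is wording in the protocol, the SAP and the reader's instructions, with the same images, reader and patients. It should be done before central reading or unblinding. The downside is that a visual one-third judgement without a baseline film is less precise than the measured ratio, so the report should give the number of patients classified by the fallback, by arm.

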### **Secondary objectives**

- To assess the efficacy of local nicardipine application via controlled-release polymers (NicaPlant®) on:

227 Incidence of new cerebral infarcts on CT of the brain performed at Day 14  $\pm$  1 post-  
228 aneurysm rupture, or before patient discharge, versus post-intervention (i.e. post clip  
229 ligation and NicaPlant® implantation) CT scan.

230

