### 269 270 **Secondary Outcome Endpoints**

271 The secondary outcome endpoints are:

- 272 • Incidence of new cerebral infarcts on CT scan at day  $14 \pm 1$ , or before patient  
273 discharge (compared with postoperative CT scan).

274

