### 856 ***Radiology***

857 Incidence of moderate to severe cerebral angiographic vasospasm assessed by digital  
858 subtraction angiography (DSA) within at  $8\pm 1$  days after aneurysm rupture where  
859 angiographic vasospasm is defined as a  $\geq 33\%$  reduction in diameter in at least one vessel  
860 segment by comparison to preoperative (pre NicaPlant® implantation) angiography and/or  
861 qualitatively assessed as moderate to severe vasospasm (in case the baseline measurement is  
862 missing). A day  $8\pm 1$  angiogram will be performed even if the patient has no clinical or

sonographic evidence of vasospasm. If the patient develops clinical or sonographic changes suggestive of vasospasm prior to day 8, and angiogram will be performed to confirm the vasospasm and the angiographic measurement will replace the one scheduled at day 8 $\pm$ 1. In case the patient develops clinical or sonographic changes suggestive of vasospasm after the day 8 $\pm$ 1 DSA and prior to patient discharge, an angiogram will be performed to confirm the vasospasm, unless not clinically indicated. Definition has been reported in section 8.4.

Computed tomography angiography (CTA) has also been used to evaluate cerebral angiographic vasospasm in this patient population, however the sensitivity and specificity of the method does not directly compare to the DSA. In order to avoid bias in assessments due to different frequency of use of DSA or CTA in the two patient groups, only DSA will be used in the current study to assess cerebral angiographic vasospasm. Patients who would have received a CTA will therefore have a higher exposition to radiation due to the DSA.

Additionally, a CT scan of the brain will be performed at screening, 36 $\pm$ 12 hours post-surgery and at day 14 $\pm$ 1, or before patient discharge, in order to identify new cerebral infarctions.

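### The CT that defines a new infarct is taken 24 to 48 h after implantation, and every infarct on it is attributed to surgery, so infarcts caused by the implants and visible by then do not enter the infarct comparison

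*Protocol*

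**What the plan says.** The secondary objective (Protocol section 2) compares the day 14 CT "versus post-intervention (i.e. post clip" ligation and implantation). The Secondary Outcome Endpoints list a single item, "Incidence of new cerebral infarcts on CT scan at day" 14±1 or before discharge, against the postoperative CT. Section 7, Visit 2, times that reference scan at 36±12 "hours from clip ligation (on NicaPlant" application), and gives it two purposes: "application) to identify surgery related ischemic lesions and for baseline assessment".

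The reading rule is in section 8, Definitions of Assessments, under the centralised neuroradiologist's assessment. Infarcts on the CT done 36±12 hours "postoperatively will be classified as surgery related and related to the respective vessel territory". For the later scan: "New infarcts (compared to such postoperative CT) in the CT scan at visit 4 will be classified as vasospasm related" or assigned to hemodynamic infarction. The definition of new infarction under Radiology in the same section uses the same reference scan.

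A pre-treatment CT also exists. Radiology states: "Additionally, a CT scan of the brain will be performed at screening". The objective, endpoint and definition do not use it as the reference.

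**The concern.** The reference scan is taken after randomisation and after treatment. Under Blinding in section 3, the theatre team checks the allocation once the aneurysm has been clipped, and only then are implants placed or not. Clipping is common to both arms; implantation is the planned difference. A between-arm difference in infarcts on the postoperative CT would then, apart from chance, reflect implantation. The reading rule nevertheless gives all of these infarcts to surgery and has no category for the implants, which the Administration section places in direct contact with the exposed vessel walls.

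Two other kinds of infarct fall under the same label, though with less weight: early vasospasm infarcts, and silent infarcts already present at entry. The exclusion criteria remove previous major cerebral damage and infarction with neurological deficit, but not a small silent infarct.

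What is at stake is interpretation. Fewer new infarcts in the implant arm would show an effect on delayed infarction. It would not show that total infarction after implantation was lower. Safety of the selected dose is also a primary objective, and infarction on the postoperative CT is not a named safety endpoint.

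**Working it through.** **Plan's own figures.** The protocol gives no infarct rate and no power for this endpoint. Its only power statement concerns the primary endpoint: 20 per arm, 70% v 20%, two-sided Fisher exact test, 84%. Exact enumeration gives 84.6%, so it reproduces. Only the 20 per arm is used below.

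**Timing of the reference scan.**
- After clipping: 36 − 12 = 24 h to 36 + 12 = 48 h.
- Latest time after rupture: clipping at 72 h (inclusion criterion 6; Visit 2) plus 48 h = 120 h, or day 5. This is the extreme of both windows.

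**What the rule does with each infarct.**

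| Infarct | On the postoperative CT? | Label | In the secondary endpoint? |
|---|---|---|---|
| Silent, already present at screening | yes | surgery related | no |
| Caused by clipping | yes | surgery related | no |
| Caused by the implants, visible by 24–48 h | yes | surgery related | no |
| Early vasospasm, visible by then | yes | surgery related | no |
| Began early, not yet visible | no | vasospasm related or hemodynamic | yes |
| Appears later | no | vasospasm related or hemodynamic | yes |

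The lesion is left out, not the patient, who stays in the analysis and still counts if a later new infarct appears.

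**Illustration with assumed rates.** Let E be the probability of an infarct new since screening and visible on the postoperative CT, and L that of one new since the postoperative CT. The planned difference is L(control) − L(implant). If E and L are taken as independent, any infarct from screening to day 14 = 1 − (1 − E)(1 − L).

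| L, control v implant | E, control v implant | Planned difference | Any infarct, control v implant | Difference |
|---|---|---|---|---|
| 40% v 20% | 10% v 10% | +20 points | 46% v 28% | +18 |
| 40% v 20% | 10% v 30% | +20 | 46% v 44% | +2 |
| 30% v 15% | 10% v 30% | +15 | 37% v 40.5% | −3.5 |
| 40% v 40% | 10% v 30% | 0 | 46% v 58% | −12 |
| 40% v 20% | 30% v 10% | +20 | 58% v 28% | +30 |

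Positive values favour the implants. Worked line, row 2: control 1 − 0.90 × 0.60 = 0.46; implant 1 − 0.70 × 0.80 = 0.44. The planned difference is unaffected by E. The total moves in either direction, and in row 3 its sign reverses.

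**Precision.** With 20 per arm, the Fisher test has 19% power for 40% v 20% and 6% for 46% v 58%. An added comparison can describe, but hardly test.

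**The case against.** The strongest reply is that the endpoint is deliberate and consistent. Objective, endpoint, definition, reading rule and analysis section all use the postoperative CT, and Visit 2 says why: to separate surgical lesions from later ones. That suits a product aimed at the complications of vasospasm. This stands. The choice of reference is neither an arithmetic error nor a contradiction.

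A reader might infer that an early implant-related infarct counts against the implant nowhere. The documents do not support that. The surgery-related label belongs to the blinded central efficacy reading. Scans are also read locally, adverse events are assessed daily, the investigator judges causality to the product, serious events are reported whatever their cause, and the DSMB sees unblinded adverse events. Disabling infarcts would also affect mRS, GOSE and mortality, which subtract no postoperative baseline. What remains is infarcts without clinical signs and the absence of a systematic imaging tabulation.

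A reader might also infer that the protocol expects vasospasm before the reference CT. It does not: angiography before day 8 is conditional on suspicion, the routine angiogram is at day 8±1, moderate or severe vasospasm at screening is excluded, and 120 h is a corner case. Lost early benefit is therefore the weaker half of the point.

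Finally, a by-arm table of postoperative infarcts could be in the SAP, which is not at hand. That is possible, but the blanket attribution is fixed in the protocol itself, and a table built on it would still call implant-related lesions surgical.

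**Conclusion.** The point holds in a limited form. The reference scan can be affected by treatment, and the rule attributes every infarct on it to surgery when implantation is the step that separates the arms. The secondary endpoint can be read as the effect on infarcts appearing after the first 24 to 48 h following clipping, not as the effect on all infarction after implantation. Unmeasured early harm, mainly clinically silent, is the main gap.

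The size is unknown. The rates in the illustration are assumed and show what the endpoint cannot detect, not what is likely to happen. Reading an early imbalance as an implant effect assumes that clipping and other care do not differ by arm, which the design intends. The change is worth making because it is cheap; the delayed-infarct endpoint itself need not be abandoned.

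**What to change.** Keep the secondary endpoint and its postoperative reference, and make four changes in the protocol and SAP:

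1. In the reading rule of section 8, replace the surgery-related label with *perioperative (surgery or implantation)*.
2. Have the same blinded neuroradiologist score the postoperative CT against the screening CT, so that infarcts present at entry are separated from perioperative ones.
3. Report new perioperative infarcts by arm, descriptively, as a named safety outcome.
4. Report any new infarct from screening CT to day 14 CT by arm, without attribution, as a supportive analysis beside the secondary endpoint, and state that the infarct conclusion is read on both.

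The scans are already scheduled, and the protocol already has all CT examinations assessed by the blinded neuroradiologist, so no new scan, reader or patient burden arises. The cost is some extra reading and analysis. The total-infarct comparison carries more surgical noise, and with 20 per arm it will be imprecise.
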